## Ethics

The study was approved by the Medical Ethical Committee of the First Affiliated Hospital of Sun Yat-sen University (Ethics no.: [2014] 88). The clinical trial is registered with the Chinese Clinical Trial Registry (Registration No.: ChiCTR-IOC-15006064, registered on 11 March 2015). Any important protocol modifications will be communicated with all relevant parties. All patients who meet the criteria will be invited to take part in the study. Patients will be given time to consider whether they wish to take part in the trial and to ask any questions. All participants can withdraw from the trial at any time without giving reason. Participants can decide if they wish to withdraw completely, in which case all collected data will be excluded from the study, or to withdraw only from further assessment or intervention wherein all collected data will be included. All participants will be reimbursed for travel expenses to encourage adherence during the follow-up phase.

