### Secondary outcome measures

Secondary outcome measures include 3D motion analysis of upper limb reach forward and reach forward and grasp motions (Figs. 1 and 2) and gait. A breif description of each secondary outcome measure is presented in Table 1. Outcome measures will be recorded at baseline, post intervention and at 3, 6 and 12 months post intervention.

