## Sample size

This study uses gait speed as the primary outcome measure for sample size calculation. An improvement in gait speed of 0.16 m/s was recommended as the minimum clinically significant difference during the first 60 days post stroke [29]. The sample size was determined by a statistical expert, using the formula:$$ N=\frac{{\left({Z}_{\alpha}+{Z}_{\beta}\right)}^2{\sigma}^2}{\delta^2}\left({Q_1}^{-1}+{Q_2}^{-1}\right) $$where *Z*
_*α*_ is normal distribution quantiles for type I error, *Z*
_*β*_ is normal distribution quantiles for type II error, σ is pooled standard deviation derived from past gait speed data, *δ* is difference in gait speed between the intervention and control group, and *Q* and *Q* are the proportions of control and intervention group.

Based on a 10% missing rate, each group requires 112 (total 224) participants to give 90% power to detect a gait speed difference of over 0.3 m/s.

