## Data analysis

Descriptive statistics will be used to describe the demographic data of each sample group. The normality of each parameter will be checked by histogram and the Kolmogorov-Smirnov test.

Chi-squared tests will be used to assess sample characteristics of gender and types of cerebral infarction.

The pre- and post-intervention differences in gait speed within individuals and between groups will be assessed by paired-samples *t* tests (two-tailed) and one-way analysis of variance (ANOVA), respectively. The comparison of 3-month, 6-month and 1-year follow-ups will be assessed by repeated-measures ANOVA.

A broadly similar approach will be used to analyse the secondary outcome measures of muscle tone, other kinematic parameters of gait, reach forward motion and reach forward and grasp motion. The kinematic parameters of the paretic side will be compared with the nonparetic side at all recording points using paired-samples *t* tests.

The Mann-Whitney *U* test will be used to test the between-group differences for the ordinal data obtained from the functional outcome measures and WHODAS 2.0.

The differences between the two groups during the follow-up phase will be assessed by the Kaplan-Meier test.

There are no planned interim analyses or stopping rules, as the power calculation has accounted for loss to follow-up. All analyses will initially be performed on an intention-to-treat basis.

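### Intention-to-treat is promised, but complete withdrawers' data are excluded, and the follow-up ANOVA in its standard form drops anyone who misses one of its visits

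*Protocol article*

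**What the plan says.** Four statements in the protocol article bear on this.

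- **Population (Data analysis).** "All analyses will initially be performed on an intention-to-treat basis".
- **Withdrawal (Ethics).** "All participants can withdraw from the trial at any time without giving reason". There are two routes. The first is: "Participants can decide if they wish to withdraw completely, in which case all collected data will be excluded from the study". The same sentence then offers the second: "or to withdraw only from further assessment or intervention wherein all collected data will be included".
- **Follow-up method (Data analysis).** "The comparison of 3-month, 6-month and 1-year follow-ups will be assessed by repeated-measures ANOVA". The between-group comparison of pre- to post-intervention change in gait speed is a separate one-way ANOVA.
- **Allowance for loss (Sample size).** The figure of 112 per group is "Based on a 10% missing rate". The Data analysis section relies on this allowance when it says the power calculation has taken loss to follow-up into account.

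The Hypotheses section places continued superiority of the VR group at 3, 6 and 12 months within the primary aim, so the follow-up comparison is not a side analysis.

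**The concern.** Intention-to-treat needs an analysis set fixed by randomisation. Under the first withdrawal route, membership depends on a decision taken later, and values already measured, including baseline and post-intervention gait speed, go with the patient. The Study design section calls the trial single-blind without saying who is blinded. The VR sessions come on top of the routine programme, so patients probably know their arm. Complete withdrawal could therefore differ between arms, in number or in kind of patient.

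The second issue is the follow-up method. Standard repeated-measures ANOVA needs a full set of the visits it analyses. A patient with two of the three follow-up values would contribute nothing to that comparison.

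What is at stake is mainly selection. If patients who do badly, or who find the programme too much, are likelier to withdraw or miss a visit, those who remain are no longer the groups that were randomised. A larger sample does not repair that. A result could also be labelled intention-to-treat when randomised patients with observed gait speed had been left out.

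**Working it through.** **Step 1: follow three patients through the text.** All are randomised and have gait speed at baseline and post intervention.

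| Patient | Ethics section | Pre/post one-way ANOVA | Follow-up repeated-measures ANOVA (standard form) |
|---|---|---|---|
| A: seen at 3 months, then withdraws completely | all data excluded | out | out |
| B: seen at 3 months, then withdraws only from further assessment | collected data included | in | out (6 and 12 months missing) |
| C: stays in the trial, misses only the 6-month visit | not affected | in | out (one value missing) |

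Patient A shows the direct contradiction: the text both requires and forbids the use of A's data. Patient B shows a second tension: the Ethics section says B's data count, yet the named method cannot use B's 3-month value. Patient C shows that no withdrawal is needed for the follow-up method to lose a patient. The last column is an inference from the method, because the article does not state how a missed visit is handled.

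**Step 2: the plan's own figure.** Inputs from the Sample size section are 112 per group, 224 in total, and 10% missing.

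- Evaluable after the allowance: 112 × (1 − 0.10) = 100.8 per group, or 201.6 in total (90%).
- The 112 itself cannot be reproduced, because neither the SD nor the type I error is given. Assuming two-sided 5% and 90% power, σ = δ × √(n/2) / (z_α + z_β) = δ × √50.4 / 3.242. This gives about 0.657 m/s for δ = 0.3 and about 0.350 m/s for δ = 0.16, the two differences named in that section. Both SDs are back-solved and neither is documented, so no power after loss is computed here.

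**Step 3: share with all three follow-up visits (illustration).** The documents give one missing rate and do not say whether it applies per visit. Suppose it does:

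- Independent across visits: 0.9³ = 0.729, so 0.729 × 224 ≈ 163 patients, about 81.6 per group.
- The same patients miss every visit: 0.90, so 201.6 patients, which equals the allowance.
- No patient misses more than one visit: 1 − 3 × 0.10 = 0.70, so about 157 patients.

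With lower independent rates, 5% per visit gives 0.95³ = 0.857 (96.0 per group), and 3% gives 0.97³ = 0.913 (102.2 per group), which stays within the allowance. Whether 10% is enough therefore depends on a rate and an overlap that the documents do not state.

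**The case against.** Exclusion is the participant's own choice, the alternative of keeping collected data is offered in the same sentence, and a participant may have a right to have data removed. That stands. A reader might infer that the plan discards everyone who withdraws, or physically erases their records; the text supports neither. It speaks of exclusion, and only for complete withdrawal. The conflict remains for those who take that route. The qualifier about performing intention-to-treat analyses initially does not remove it, since the exclusion applies to the first analysis as much as to any later one. Running intention-to-treat first and other sets afterwards is ordinary practice.

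Against the second part, the article nowhere says that incomplete patients are dropped. A statistical analysis plan that is not shown could impute before the ANOVA, which would fit the intention-to-treat sentence. That also stands, and is why this part is put as an inference. It does not make the named method a good choice for repeated visits with expected loss.

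The 10% may also be meant as total loss over follow-up, which would leave 90% complete. The documents allow that reading, so it cannot be said that the allowance fails.

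Three further inferences go too far. The whole trial is not a completers' analysis, because the pre/post one-way ANOVA keeps a patient who misses a later visit. The trial should not be called unblinded, since it is described as single-blind; the argument needs only that patients probably know their arm. Finally, a reader might put a number on lost power or on bias. That would need an SD, withdrawal rates by arm and outcome differences that the documents do not give.

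**Conclusion.** The point holds in two parts of different strength.

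1. **Certain from the text.** Excluding all data of patients who withdraw completely after randomisation is incompatible with the intention-to-treat promise. It affects every comparison, including pre/post gait speed. Its size depends on how many take that route in each arm, which cannot be known from the documents.
2. **Inferred from the named method.** Standard repeated-measures ANOVA would lose patients with a missed visit from the 3-, 6- and 12-month comparison, including partial withdrawers whose data are meant to be included. The pre/post one-way ANOVA is not affected. If 10% were missing at each visit, 73% would be complete under independence and 90% under full overlap.

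The main harm is possible selection between arms, with some loss of information already collected. No power or bias figure is claimed.

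**What to change.** 1. **Follow-up analysis.** Replace repeated-measures ANOVA of gait speed with a likelihood-based mixed model with arm, visit, arm-by-visit interaction and baseline gait speed, using every available visit of every randomised patient in the assigned arm. Patients B and C above would then contribute what was measured. The model relies on missingness being explained by the observed data, which should be stated.
2. **Withdrawal.** Make stopping further participation, with collected data retained, the default meaning of withdrawal. Exclude data only on an explicit, separate request. Report the number of such exclusions by arm, and add a sensitivity analysis that varies the assumed outcomes of these patients by arm. The mixed model cannot recover data that have been excluded, so this step is needed as well as the first.

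**Cost.** A small ethics amendment to the withdrawal wording, with patients already enrolled keeping the option they were offered, a changed line in the Data analysis section, and slightly more analysis work. No extra visits or patients are needed.

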## Outcome measures

### Primary outcome measure

Gait speed, assessed by the 10-m Walk Test, is the primary outcome measure.

### Secondary outcome measures

Secondary outcome measures include 3D motion analysis of upper limb reach forward and reach forward and grasp motions (Figs. 1 and 2) and gait. A breif description of each secondary outcome measure is presented in Table 1. Outcome measures will be recorded at baseline, post intervention and at 3, 6 and 12 months post intervention.

**Fig. 1 Fig1:**
[figure not shown]
**a** Starting position of reach forward assessed by Vicon. **b** End position of reach forward motion

**Fig. 2 Fig2:**
[figure not shown]
**a** Starting position of reach and grasp motion assessed by Vicon. **b** End position of each and grasp motion

**Table 1 Tab1:** Descriptions of the secondary outcome measures

Secondary outcome measures	Descriptions
Action Research Arm Test (ARAT)	The ARAT [41] is a 19-item observational test. It is divided into 4 subtests (grasp, grip, pinch and gross arm movement). Performance on each item is rated on a 4-point ordinal scale ranging from: 0 – can perform no part of test; 1 – performs test partially; 2 – completes test, but takes abnormally long or has great difficulty; 3 – performs test normally
Instrumental Activities of Daily Living (IADL)	The IADL [24] is a functional disability scale which assesses functional level by asking whether a person receives personal help with activities of daily living, such as using the telephone, getting to places outside the house, grocery shopping, preparing meals, doing housework or handyman work, laundry, taking medications and managing finances
Gait analysis	Spatiotemporal gait parameters, joint angles and moment of the lower limbs will be recorded by Vicon Motion Systems, Oxford, UK. Parameters will be recorded at: (1) maximum hip and knee extension during stance phase, (2) maximum flexion at the hip and knee joints during the swing phase, (3) plantarflexion during push-off and (4) dorsiflexion during swing phase of the gait cycle. Spatiotemporal gait parameters of gait speed, cadence, stride length, stride time and step length will be recorded
Upper limb motion analysis	Dynamic changes of shoulder and elbow motions will be measured by Vicon Motion Systems. Parameters recorded during reach forward task (Fig. 1a, b) are: (1) movement time (s), (2) peak velocity (m/s), (3) shoulder amplitude (^o^) and (4) elbow amplitude (^o^)
	Parameters of: (1) movement time (s), (2) peak velocity (m/s), (3) shoulder amplitude (^o^) and (4) elbow amplitude (^o^), (5) supination peak velocity (m/s) and (6) pronation peak velocity (m/s) during reach forward and grasp (Fig. 2a, b)
	Motions for the paretic and nonparetic arms will be recorded and compared
Short Orientation Memory Concentration Test (SOMCT)	The SOMCT [25] is a validated measurement for cognitive impairment. It is a short assessment of cognitive function composed of 6 items
Mini Mental Status Examination (MMSE)	The MMSE is a brief screening tool that provides a quantitative assessment of cognitive impairment and assesses changes over time. It was originally developed as part of an assessment for dementia and was validated for use in patients with acute stroke [26]
Fugl-Meyer Assessment of Motor Recovery (FMA)	The FMA [27] is a validated evaluation tool for motor function, balance and joint function in post-stroke hemiplegic patients
Berg Balance Scale (BBS)	The BBS [42] was developed to assess static and dynamic balance abilities. It is composed of 14 simple balance-related tasks including sit to stand, stand to sit and standing on one foot
Grip strength	Grip strength will be measured with a Jamar ® hydraulic hand dynamometer
Muscle tone	Changes of muscle tone (bicep brachii, brachioradialis, extensor digitorum, flexor carpi radialis and flexor carpi ulnaris) pre and post treatment will be measured by the MyotonPRO® hand-held device whose use in the stoke population has been validated [43]
World Health Organisation Disability Assessment Schedule 2.0 (WHODAS)	The WHODAS is a standardised measurement of health and disability across cultures [44]. It captures the level of functioning in 6 domains of life: cognition, mobility, self-care, getting along, life activities and participation. It has been validated for use in people with chronic illnesses [45]

### Outcome assessments

Outcome assessments will be conducted by the dedicated assessment team. The team consists of occupational therapists, physiotherapists, physicians and engineers who are specifically trained to perform the outcome assessments. The institute is a World Health Organisation Collaborating Centre and is responsible for delivering training on the use of the outcome measure tools to health care professionals.

## Sample size

This study uses gait speed as the primary outcome measure for sample size calculation. An improvement in gait speed of 0.16 m/s was recommended as the minimum clinically significant difference during the first 60 days post stroke [29]. The sample size was determined by a statistical expert, using the formula:$$ N=\frac{{\left({Z}_{\alpha}+{Z}_{\beta}\right)}^2{\sigma}^2}{\delta^2}\left({Q_1}^{-1}+{Q_2}^{-1}\right) $$where *Z*
_*α*_ is normal distribution quantiles for type I error, *Z*
_*β*_ is normal distribution quantiles for type II error, σ is pooled standard deviation derived from past gait speed data, *δ* is difference in gait speed between the intervention and control group, and *Q* and *Q* are the proportions of control and intervention group.

Based on a 10% missing rate, each group requires 112 (total 224) participants to give 90% power to detect a gait speed difference of over 0.3 m/s.

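### The sample-size section cites 0.16 m/s as the clinically important difference but claims 90% power for 0.3 m/s; the two are not reconciled, and if 0.3 m/s is the design difference, power at 0.16 m/s is about 41%

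*Protocol article*

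**What the plan says.** Gait speed on the 10-m Walk Test is the only primary outcome (protocol article, Primary outcome measure). The Sample size section opens with a clinical benchmark: "An improvement in gait speed of 0.16 m/s was recommended as the minimum clinically significant difference during the first 60 days post stroke". It then prints a two-group formula in which δ "is difference in gait speed between the intervention and control group", σ is a pooled SD taken from earlier gait speed data, and Z_α "is normal distribution quantiles for type I error". No value is attached to δ, σ or Z_α at the formula. The section ends by saying that, with 10% missing, "each group requires 112 (total 224) participants to give 90% power to detect a gait speed difference of over 0.3 m/s".

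The Randomisation section gives 1:1 allocation. The Data analysis section plans to compare changes in gait speed from before to after the intervention, within patients by paired t tests and between groups by one-way ANOVA. It attaches two-tailed testing only to the paired t tests.

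**The concern.** The section gives one figure for what matters clinically and a different, larger one for what the trial can detect. The second is 1.875 times the first (0.3/0.16), and no reason is given. Sample size varies with the inverse square of the difference, so this gap corresponds to a factor of about 3.5 in patients (1.875² = 3.52).

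A reader will use the stated detectable difference to interpret a non-significant result. If the trial was truly sized on 0.3 m/s, it is more likely than not to miss a real effect equal to its own benchmark. The Background criticises earlier virtual reality studies for inadequate sample size, so the same weakness here would matter. If the trial was sized on 0.16 m/s, the design is sound and the published sentence undersells it. The two cases call for different corrections, and the article does not show which one applies.

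**Working it through.** **Inputs stated in the article.** Power 90%; 1:1 allocation (Q₁ = Q₂ = 0.5); 10% missing; 224 randomised, so 224 × 0.9 = 201.6 evaluable (100.8 per arm); differences of 0.16 and 0.3 m/s.

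**Inputs not stated.** SD, alpha and sidedness. Two-sided 5% is assumed below; one-sided 5% and two-sided 1% are shown as a range. The target of over 0.3 m/s is taken at its boundary, 0.3 m/s.

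**1. Can 224 be reproduced?** Not forwards, because σ is missing. With equal groups the article's formula becomes

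N = (Z_α + Z_β)² σ²/δ² × (2 + 2) = (1.960 + 1.2816)² × 4 × σ²/δ² = 42.03 σ²/δ².

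Setting N = 201.6 and solving, σ = δ × √(201.6/42.03) = 2.190 δ:

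- δ = 0.3 m/s gives σ = 0.657 m/s
- δ = 0.16 m/s gives σ = 0.350 m/s

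Put back into the formula, each pair returns the published size:

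- σ = 0.657, δ = 0.3: 42.03 × 0.4316/0.09 = 201.6, and 201.6/0.9 = 224.0
- σ = 0.35, δ = 0.16: 42.03 × 0.1225/0.0256 = 201.1, and 201.1/0.9 = 223.5

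This agreement is circular, since each σ was solved from 224. It shows only that both differences can be made to fit.

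**2. Power at 0.16 m/s if the 0.3 m/s statement is true.** The SD and the sample size cancel:

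power = Φ[(Z_α + Z_β) × 0.16/0.3 − Z_α]

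| Assumption | Calculation | Power at 0.16 m/s | Implied SD at δ = 0.3 | Implied SD at δ = 0.16 |
|---|---|---|---|---|
| Two-sided 5% | Φ(3.2415 × 0.5333 − 1.960) = Φ(−0.231) | 41% | 0.657 | 0.350 |
| One-sided 5% | Φ(2.9264 × 0.5333 − 1.645) = Φ(−0.084) | 47% | 0.728 | 0.388 |
| Two-sided 1% | Φ(3.8574 × 0.5333 − 2.576) = Φ(−0.519) | 30% | 0.552 | 0.294 |

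The implied SDs are δ × √(201.6/4)/(Z_α + Z_β) = δ × 7.099/(Z_α + Z_β). A noncentral t calculation at two-sided 5% also gives 40.9%. If the design difference lies above 0.3 m/s, power at 0.16 m/s is lower still.

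On this branch (σ = 0.657), 90% power at 0.16 m/s would need 42.03 × 0.4316/0.0256 ≈ 709 evaluable. That is 355 per arm, 395 per arm after 10% missing, or about 790 in total.

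**3. Power at 0.3 m/s if 0.16 m/s was the design difference (σ = 0.35, two-sided 5%).** Φ(3.2415 × 0.3/0.16 − 1.960) = Φ(4.12), which is over 99.9%. For 90% power at 0.3 m/s, 42.03 × 0.1225/0.09 ≈ 57 evaluable would do. That is 29 per arm, 33 per arm after 10% missing, or about 66 in total.

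**4. Range over the unknown SD.** With 100.8 evaluable per arm and two-sided 5%, power at 0.16 m/s is 97% for an SD of 0.30, 90% for 0.35, 81% for 0.40, 62% for 0.50, 47% for 0.60 and 41% for 0.657.

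**5. Which SD is more plausible?** Gait speed cannot be negative. With an SD of 0.657, mean minus two SDs stays above zero only if mean speed exceeds 2 × 0.657 ≈ 1.31 m/s. That looks high for patients within a month of stroke, some of whom walk only with assistance (Sample population). It is a reason to check the 0.3, not proof of an error: the article reports no gait speed data, and the argument does not apply if σ is the SD of change, which can be negative.

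**The case against.** The best defence is that nothing in the section is shown to be miscalculated. The 0.16 m/s figure is worded as an improvement, while 0.3 m/s is the only value tied to power and δ is a contrast between groups. A trial may cite a clinical benchmark and still be sized on a larger expected effect. This stands: the two figures are not a strict contradiction. What remains is that 0.16 m/s is the only clinical anchor offered, 0.3 m/s has no justification, and both appear in the same short section.

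A second defence is that a journal article condenses a fuller protocol, and a statistician is said to have done the calculation. This also stands: the missing SD, alpha and sidedness are not a fault in themselves. They limit what can be concluded here.

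A reader might infer that 224 was really sized on 0.16 m/s, because an SD of 0.35 m/s reproduces it so closely. The documents do not support that. The 0.35 is back-solved from 224, and an SD of 0.66 m/s reproduces 224 for 0.3 m/s equally well. Nor can two-sided 5% be called a stated input.

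A reader might also infer that σ is the wrong kind of SD, since the analysis concerns changes ("The pre- and post-intervention differences in gait speed within individuals and between groups will be assessed by paired-samples" t tests and ANOVA). Earlier gait speed data could supply either an SD of speed or an SD of change, so no mismatch is shown; the text only fails to say which.

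Finally, whether a null result excludes 0.16 m/s will depend on the observed confidence interval, not on the planning sentence. That is true, but the planning sentence is what readers will quote.

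**Conclusion.** The point holds as an unreconciled design figure, not as a demonstrated arithmetic error. Taken at its word, the power statement leaves the trial with about 41% power at its own clinical benchmark. That figure rests on the stated 90% power at 0.3 m/s and on an assumed two-sided 5%. It does not depend on the SD, and it stays below 50% across the alphas tried (30% to 47%). If instead 0.16 m/s produced 224, the power sentence is wrong and understates the design, with over 99.9% power at 0.3 m/s. The documents cannot decide between the two. The large SD implied by 0.3 m/s is a reason to check, and no more than that.

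**What to change.** Retrieve the original calculation and restate the paragraph with one consistent set: between-group difference, SD, alpha, sidedness, power and missing rate. Say whether the SD is of gait speed or of its change, and match it to the primary analysis.

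- If the file shows 0.16 m/s, correct the power sentence to that difference with the SD actually used (about 0.35 m/s if two-sided 5% was used).
- If the file shows 0.3 m/s, keep 224, say why 0.3 m/s was chosen, give the SD used, and report the power at 0.16 m/s (about 41% at two-sided 5%). Add that a non-significant result should not be read as excluding a clinically important benefit.

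The cost is one corrected paragraph, as an amendment or published correction, and possibly a less favourable stated power. Recruitment does not change.
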